### Criteria for discontinuing or modifying allocated interventions {11b}

If participants request to withdraw from the trial, we will discontinue the allocated intervention for a given trial participant.

### Strategies to improve adherence to interventions {11c}

Adherence to interventions primarily refers to patient self-management adherence.

### Relevant concomitant care permitted or prohibited during the trial {11d}

No concomitant care or interventions will be permitted during this trial.

### Provisions for posttrial care {30}

If a participant suffers harm from this trial, he/she will receive financial compensation accordingly. The amount of compensation will be determined jointly by consulting the relevant departments and the participant.

### Outcomes {12}

#### Primary outcome measures

The primary outcome of this study is the incidence of hypoxia (75% ≤ SpO_2_ < 90% for <60 s) in the two groups from the beginning to the end of the operation.

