### Objectives {7}

Our aim is to investigate whether an additional capnographic monitoring-based intervention can reduce hypoxia incidence in older patients undergoing gastrointestinal endoscopy under sedation. Our primary objective is to measure the incidence of hypoxia (75% ≤ SpO_2_ < 90% for < 60 s). Our secondary objective is to measure the incidences of subclinical respiratory depression (90% ≤ SpO_2_ < 95%), severe hypoxia (SpO_2_ < 75% or 75% ≤ SpO_2_ < 90% for ≥60 s), and other adverse events (AEs) recorded via tools proposed by the World Society of Intravenous Anesthesia International Sedation Task Force. We predict that additional capnographic monitoring of ventilatory activity will reduce hypoxia incidence during propofol sedation for gastrointestinal endoscopy in older patients. Our aim is to provide credible evidence regarding reduced hypoxia incidence in older patients.

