#### Secondary outcome measures

The secondary outcomes comprise the following:The incidence of subclinical respiratory depression (90% ≤ SpO_2_ < 95%) in the two groups from the beginning to the end of the operation.The incidence of severe hypoxia (SpO_2_ < 75% or 75% ≤ SpO_2_ < 90% for ≥60 s) in the two groups from the beginning to the end of the operation.The incidence of other AEs recorded via tools proposed by the World Society of Intravenous Anesthesia International Sedation Task Force.

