**Others**						
Gastroscope procedure time				**×**		
Combined medication	**×**	**×**	**×**	**×**	**×**	**×**

When the participants will enter the gastrointestinal endoscopic operating room, they will be screened for eligibility by the investigator. If they meet the inclusion criteria but not the exclusion criteria, the investigator will provide them with the fully informed consent form. After signing the informed consent form, the patients will be allocated to either the capnographic monitoring group or the control group via the central randomization system.

In the capnographic monitoring group, the criteria for apnea is the absence of exhaled CO_2_; altered ventilation is defined as end-tidal CO_2_ reduced by more than half of the baseline, as shown by the capnogram; and the definition of hypoxia is 75%<SpO_2_ < 90%, <60s. In the control group, hypoxia is defined as SpO_2_ <90%.

In both the groups, any sign of apnea, altered ventilation, or hypoxia that prompts an intervention will comprise (i) increasing oxygen supplementation, (ii) a chin lift or jaw thrust maneuver, (iii) insertion of the oropharyngeal or nasopharyngeal airway with a chin lift or jaw thrust maneuver, (iv) artificial mask ventilation, and (v) tracheal intubation.

The duration of surgery is defined as the time from the beginning to the end of the gastrointestinal endoscopy, excluding the time of resuscitation.

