#### Statistical analysis plan

All statistical analyses in this trial will be programmed and calculated using Statistical Package for the Social Sciences version 23.0 (IBM Inc., Armonk, NY, USA). The normally distributed baseline continuous data will be represented by mean (standard deviation [SD]) and compared by using an unpaired *t*-test. The non-normally distributed continuous data will be presented as median (interquartile range [IQR]) and compared by using Mann–Whitney *U* test. We will use χ^2^ test, continuity correction *χ*^2^ test, or Fisher’s exact test to analyze the categorical variables. We intend to compare the incidences of hypoxia, subclinical hypoxia, severe hypoxia, and total hypoxia of the participants during gastrointestinal endoscopy under sedation via *χ*^2^ test, continuity correction *χ*^2^ test, or Fisher’s exact test.

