### Methods for additional analyses (e.g., subgroup analyses) {20b}

The association between the baseline characteristics and intervention and the risk of total hypoxia cumulative incidence was examined using univariable- and multivariable-adjusted logistic regression models. The results were presented as the odds ratios and corresponding 95% confidence intervals.

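### As worded, the primary outcome leaves out prolonged desaturation and possibly desaturation below 75%, so shortening a severe episode can add a primary event; the two arms are also given different hypoxia definitions

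*Protocol article*

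**What the plan says.** **Primary outcome.** Objectives {7} and Primary outcome measures agree: "Our primary objective is to measure the incidence of hypoxia (75% ≤ SpO_2_ < 90% for < 60 s") and "The primary outcome of this study is the incidence of hypoxia (75% ≤ SpO_2_ < 90% for <60 s"). The event has a floor in depth (75%) and a ceiling in duration (60 s).

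**Severe hypoxia.** This is a separate secondary outcome: "The incidence of severe hypoxia (SpO_2_ < 75% or 75% ≤ SpO_2_ < 90% for ≥60 s) in the two groups".

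**Total hypoxia.** The Statistical analysis plan section adds a fourth category: "We intend to compare the incidences of hypoxia, subclinical hypoxia, severe hypoxia, and total hypoxia of the participants". Methods for additional analyses {20b} models it: "the risk of total hypoxia cumulative incidence was examined using univariable- and multivariable-adjusted logistic regression models". It is not among the listed outcomes and is not defined.

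**Definitions by arm.** Below Table 3, in Participant timeline {13}, the text for the capnography group reads "the definition of hypoxia is 75%<SpO_2_ < 90%, <60s". The next sentence reads "In the control group, hypoxia is defined as SpO_2_ <90" per cent, with no floor and no duration limit.

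**Recording form.** Table 2, Step 2, lists brief desaturation and severe or prolonged desaturation as separate boxes, and the recorder may tick every box that applies.

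**Sample size {14}.** The control rate is about 8% for hypoxia, without band or duration, and is assumed to halve to 4%.

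**The concern.** The trial asks whether capnography lowers the incidence of hypoxia. The Discussion gives the mechanism: early detection and timely action should make severe hypoxia less frequent. An outcome capped at 60 s and 75% does not fit that mechanism well. If an 85% desaturation lasts 90 s in control and the same patient would have had 85% for 30 s with capnography, the patient has gained, yet the count goes from no primary event to one.

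The text below Table 3 pulls the other way. If its two definitions were used for counting, a severe event would count in control but not with capnography, which would favour capnography. Only participants are blinded (Who will be blinded {17a}), so an unclear counting rule would be applied by staff who know the arm.

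At stake is the primary test: its power, and in extreme cases its direction.

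**Working it through.** **1. Who is a primary event?** Setting the definitions side by side:

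| Patient's only episode | Primary outcome | Severe (secondary) | Below Table 3, capnography | Below Table 3, control |
|---|---|---|---|---|
| 85% for 30 s | yes | no | yes | yes |
| 85% for 90 s | no | yes | no | yes |
| nadir 70%, one label per episode | no | yes | no | yes |
| nadir 70%, passage through 75-90% also counted | yes | yes | yes | yes |

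The second row follows from the wording alone. The last two rows depend on a rule that the protocol does not give.

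**2. The plan's own sample size.** Inputs from Sample size {14}: 8% v 4%, 1:1, 90% power, two-sided 5%, 10% dropout.

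n = [1.960·√(2·0.06·0.94) + 1.282·√(0.08·0.92 + 0.04·0.96)]² / 0.04² = 739 per arm. With continuity correction, n' = (n/4)·[1 + √(1 + 4/(n·0.04))]² = 788. Dropout: 788/0.9 = 876 per arm, 1752 in total, against about 1800 stated. The arithmetic is sound; the point concerns the event, not the number.

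**3. Illustrative power.** Evaluable per arm: 900 × 0.9 = 810. Assumptions that are not in the protocol:
- any SpO2 below 90% falls from 8% to 4%;
- each patient is classed by worst category, so in each arm brief = any − severe;
- the severe rates are as listed.

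Power is exact: binomial probabilities are summed over outcomes where the uncorrected chi-square test rejects at two-sided 5%.

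| Severe, control → capnography | Capped primary | Power |
|---|---|---|
| 0% → 0% | 8% v 4% | 93% |
| 1% → 0.5% | 7% v 3.5% | 89% |
| 2% → 1% | 6% v 3% | 84% |
| 2% → 0.5% | 6% v 3.5% | 66% |
| 2% → 0% | 6% v 4% | 46% |
| 3% → 0% | 5% v 4% | 16% |
| 4% → 0% | 4% v 4% | no signal |

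Hand check of the second row by normal approximation: SE under the null = √(2·0.0525·0.9475/810) = 0.01108; SE under the alternative = 0.01105; (0.035 − 1.960·0.01108)/0.01105 = 1.20, giving 0.885, close to the exact 0.893.

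**4. Extreme case.** Suppose any hypoxia is 8% in both arms and capnography turns a 4% severe rate entirely into brief episodes. The capped primary reads 4% v 8%, with a 93% chance of a significant result against capnography. The mirror case (severe 0% v 4%) gives a 93% chance of a significant result in its favour. Both need half of all hypoxia in one arm to be severe and none in the other.

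**5. The alternative reading of the 8%.** If 8% to 4% describes the capped event, as the protocol's own definition of hypoxia suggests, the primary compares 8% v 4% as planned and power is 93%.

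**The case against.** The strongest reply has four parts.

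- **Overlap.** Nothing makes the categories mutually exclusive, and the Table 2 form allows both boxes to be ticked. A patient who drops below 75% passes through 75-90% and may have separate brief episodes. A reader might infer that every severe case is scored as a success; the documents do not establish that. The single sustained episode of 60 s or more remains outside the primary outcome on the wording.
- **Power.** The losses appear only if the 8% is assigned to any SpO2 below 90%, and the large ones only if severe hypoxia falls much faster than brief hypoxia. Proportional falls cost little (93% to 89% or 84%). The population is ASA I-II with the exclusions of Table 1, and no severe rate is given, so large severe shares cannot be called likely. This stands.
- **Visibility.** A reader might infer that a rise in severe hypoxia would go unseen. It would not: severe and total hypoxia are compared between arms in the Statistical analysis plan section. Those comparisons would not, however, change the primary test.
- **Deliberate choice.** The band matches the minor-risk category of the Table 2 tool. That explains its origin, but a form that grades adverse events by severity does not make one middle grade a suitable efficacy outcome.

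The arm-specific definitions may be meant only as triggers for intervention. The protocol does not say so, and it does not say that they are used for counting; the bias toward capnography is therefore conditional.

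**Conclusion.** The point holds as a defect in how the primary event is defined. By its wording the outcome omits patients whose only event is prolonged desaturation and, on a one-label-per-episode reading, those whose only episode falls below 75%. It can therefore count against the benefit that the Discussion expects. The unequal definitions below Table 3 leave the counting rule unsettled between arms.

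The size cannot be determined from the protocol. Under worst-category scoring, with 8% to 4% assigned to any SpO2 below 90%, power at 810 per arm runs from 89% (severe 1% to 0.5%) to 16% (severe 3% to 0%), against 93% for the uncapped event. If 8% to 4% belongs to the capped event, there is no loss.

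The stronger statement that the trial cannot answer its question, or that its result will be reversed, is not supported: it needs severe rates and a scoring rule that the protocol does not contain.

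**What to change.** By dated protocol amendment and registry update, before any look at outcomes by arm:

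1. Define the primary outcome as at least one SpO2 below 90%, of any depth or duration, from the beginning to the end of the procedure, counted by the same rule in both arms.
2. Define total hypoxia as exactly this event, excluding the 90-95% band.
3. Keep brief and severe hypoxia as secondary components, and state whether a patient can count in both or is classed by worst category.
4. State which definition the 8% in Sample size {14} refers to. If it is any SpO2 below 90%, the planned number stands; if not, recheck the calculation for the new event.
5. Reconcile Objectives {7}, both outcome sections, the text below Table 3, the Statistical analysis plan section and Methods for additional analyses {20b}. For the text below Table 3, say whether the definitions serve for counting or only as triggers for intervention.

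The cost is small in data and analysis: the saturation outcomes are already collected and a total-hypoxia comparison is already planned. The real downside is a documented change of primary outcome in an ongoing trial that is open to staff, so the timing and the absence of any look by arm must be on record.

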#### Secondary outcome measures

The secondary outcomes comprise the following:The incidence of subclinical respiratory depression (90% ≤ SpO_2_ < 95%) in the two groups from the beginning to the end of the operation.The incidence of severe hypoxia (SpO_2_ < 75% or 75% ≤ SpO_2_ < 90% for ≥60 s) in the two groups from the beginning to the end of the operation.The incidence of other AEs recorded via tools proposed by the World Society of Intravenous Anesthesia International Sedation Task Force.

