### Eligibility criteria {10}

This clinical trial has three centers that recruited patients. A summary of the inclusion and exclusion criteria is presented in Table 1.

**Table 1 Tab1:** Inclusion/exclusion criteria

Inclusion criteria	Exclusion criteria
1) Aged ≥65 and <80 years	1) Coagulation disorders or a tendency of nose bleeding
2) Scheduled to undergo gastrointestinal endoscopy procedure with sedation	2) An episode/exacerbation of congestive heart failure that requires a change in medication, diet, or hospitalization from any cause in the past 6 months
3) Signed the informed consent form	3) Severe aortic stenosis or mitral stenosis
4) American Society of Anesthesiologists (ASA) classification I-II	4) Cardiac surgery involving thoracotomy (e.g., coronary artery bypass graft, valve replacement surgery) in the past 6 months
	5) Acute myocardial infarction in the past 6 months
	6) Acute arrhythmia (including any tachycardia or bradycardia) with fluid of hemodynamics instability
	7) Diagnosed with chronic obstructive pulmonary disease or current other acute or chronic lung disease requiring supplemental chronic or intermittent oxygen therapy
	8) Preexisting bradycardia (heart rate <50/min), or hypoxia (SaO_2_ < 90%)
	9) Need supplemental oxygen because of preexisting diseases
	10) Emergency procedure or surgery
	11) Multiple trauma
	12) Upper respiratory tract infection
	13) Allergy to propofol or tape and adhesives

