**Step 5: Assign a SEVERITY rating to the adverse event(s) associated with this sedation encounter.**				
If there are any options checked in the Sentinel columns above, then this is a Sentinel adverse event^j^.				
If the most serious option(s) checked above are Moderate risk, then this is a Moderate risk adverse event^k^.				
If the most serious option(s) checked above are Minor risk, then this is a Minor risk adverse event^l^.				
If the most serious option(s) checked above are Minimal risk, then this is a Minimal risk adverse event^m^.				

Footnotes:

^a^ “Sub-clinical respiratory depression” is defined as capnographic abnormalities suggesting respiratory depression that do not manifest clinically

^b^ “Paradoxical response” is defined as unanticipated restlessness or agitation in response to sedatives

^c^ “Recovery agitation” is defined as abnormal patient affect or behaviors during the recovery phase that can include crying, agitation, delirium, dysphoria, hallucinations, or nightmares

^d^ “Prolonged recovery” is defined as failure to return to baseline clinical status within 2 hours

^e^ “Failed sedation” is defined as inability to attain suitable conditions to humanely perform the procedure

^f^ Alteration in vitals signs (bradycardia, tachycardia, hypotension, hypertension) is defined as a change of >25% from baseline

^g^ “Cardiovascular collapse/shock” is defined as clinical evidence of inadequate perfusion

^h^ Examples of “escalation of care” include transfer from ward to intensive care, and prolonged hospitalization

^i^ “Pulmonary aspiration syndrome” is defined as known or suspected inhalation of foreign material such as gastric contents into the respiratory tract associated with new or worsening respiratory signs

^j^ “Sentinel” adverse events are those critical enough to represent real or serious imminent risk of serious and major patient injury. Once recognized, they warrant immediate and aggressive rescue interventions. Once clinically concluded, they warrant immediate reporting within sedation care systems and the highest level of peer scrutiny for continuous quality improvement

^k^ “Moderate” adverse events are those that, while not sentinel, are serious enough to quickly endanger the patient if not promptly managed. Once clinically concluded, they warrant timely reporting within sedation care systems and periodic peer scrutiny for continuous quality improvement

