**Research outcome measures**						
Hypoxia		**×**	**×**	**×**		
Sub-clinical hypoxia		**×**	**×**	**×**		
Severe hypoxia		**×**	**×**	**×**		
Adverse event		**×**	**×**	**×**		

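### The subclinical respiratory depression outcome has no baseline reference, so an eligible patient still at 90–94% when the outcome window opens counts as an event without any change

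*Protocol article*

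**What the plan says.** All references are to the protocol article.

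- **Outcome.** The section Secondary outcome measures lists "The incidence of subclinical respiratory depression (90% ≤ SpO_2_ < 95%) in the two groups from the beginning to the end of the operation". It states no minimum duration, no reference to a starting value and no rule for patients already in the band. Objectives {7} names the same outcome.
- **Eligibility.** Table 1, exclusion 8 reads "Preexisting bradycardia (heart rate <50/min), or hypoxia (SaO_2_ < 90" (per cent). No criterion sets a limit at 95%. Other criteria bear on low resting saturation without a threshold: "Diagnosed with chronic obstructive pulmonary disease or current other acute or chronic lung disease requiring supplemental chronic or intermittent oxygen therapy", "Need supplemental oxygen because of preexisting diseases" and, on the inclusion side, "American Society of Anesthesiologists (ASA) classification I-II".
- **Window.** Participant timeline {13} states: "The duration of surgery is defined as the time from the beginning to the end of the gastrointestinal endoscopy, excluding the time of resuscitation". In Table 3 the row "Sub-clinical hypoxia" is marked at sedative induction, procedure start and procedure over, and not at arrival. Vital signs are marked at every time point, including arrival and induction.
- **Oxygen.** Intervention description {11a} gives 2 L/min by nasal cannula. Concealment mechanism {16b} says both groups use the same cannula.
- **Analysis.** The section Statistical analysis plan compares the crude proportions with a χ² or Fisher's exact test.

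**The concern.** The eligibility floor is 90% and the event band reaches up to 95%, so the two overlap between 90% and 95%. The name of the outcome implies that something happened to the patient under sedation, but the definition does not require it. A patient who enters the window at 93% and stays there is an event.

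The other two saturation outcomes do not share this problem. Primary events and severe hypoxia need a value below 90%, and exclusion 8 already removes patients who start there. Only the subclinical band lacks that protection.

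At stake is a named secondary objective. Capnography cannot prevent a value that was present before sedation, so these patients add the same expected number of events to each arm. The reported incidence is too high and the risk ratio is too close to 1. The article also analyses total hypoxia without defining it. If that composite includes the subclinical band, the same misclassification would carry into the logistic models under Methods for additional analyses {20b}.

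**Working it through.** **1. The plan's own figure.** Inputs from Sample size {14}: 8% versus 4%, two-sided α 0.05, power 0.90, 1:1, 10% dropout.

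- Uncorrected n per arm = [1.960·√(2·0.06·0.94) + 1.2816·√(0.08·0.92 + 0.04·0.96)]² / 0.04² = 738.7, so 739.
- With continuity correction: (738.7/4)·[1 + √(1 + 4/(738.7·0.04))]² = 788 per arm.
- After dropout: 788/0.90 = 876 per arm, 1752 in total. This agrees with about 1800 to within 3%.

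The sample size rests on the primary outcome alone, so the present point does not alter it. Evaluable patients per arm: 900 × 0.90 = 810.

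**2. Can a non-event be counted?** Follow a patient at 93%.

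- Exclusion 8 does not apply, since 93% is not below 90%.
- The arrival reading is not counted, since the outcome row in Table 3 has no mark there.
- If the value is still 93% at induction or procedure start, it lies in the band inside the window, and the patient is an event.
- If oxygen has raised it to 95% or more by then and it stays there, the patient is not an event.

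So the misclassification is possible, but only for values that persist into the window.

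**3. How far would it dilute the contrast?** Let b be the share in the band from the start, equal in both arms by randomisation, and p the true new-onset rate among the rest. Then observed rate = b + (1 − b)p. The absolute difference shrinks by the factor (1 − b), and the risk ratio moves toward 1.

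Neither b nor p is in the documents. The values below are assumptions: b from 2% to 10%, and p = 20% (control) versus 12% (capnography). Power is the two-sided normal approximation with 810 per arm.

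| b | Automatic events per arm (810·b) | Control | Capnography | Difference (points) | Risk ratio | Power |
|---|---|---|---|---|---|---|
| 0 | 0 | 20.0% | 12.0% | 8.0 | 0.60 | 0.99 |
| 2% | 16 | 21.6% | 13.8% | 7.8 | 0.64 | 0.99 |
| 5% | 40 | 24.0% | 16.4% | 7.6 | 0.68 | 0.97 |
| 10% | 81 | 28.0% | 20.8% | 7.2 | 0.74 | 0.92 |

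**4. Sensitivity to the assumed effect.**

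- 20% versus 15%: power falls from 0.76 (b = 0) to 0.71 (2%), 0.64 (5%) and 0.54 (10%).
- 16% versus 8%: power falls from 0.999 (b = 0) to 0.985 (5%) and 0.947 (10%).

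The loss is appreciable if the true effect on this outcome is modest, and small if it is large.

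**The case against.** **Timing.** A reader might infer that patients are counted before any sedation. The documents do not support that. Counting runs over the operation, or from induction at the earliest by Table 3. This objection stands in full and limits the point to values that persist into the window.

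**Size.** Oxygen at 2 L/min, restriction to ASA I–II, and the exclusions for COPD, oxygen need, upper respiratory infection and recent heart failure exacerbation all reduce the number who could enter the window at 90–94%. The share may be negligible. This stands as a limit on size. It does not close the gap, because none of these criteria sets a limit at 95%.

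**Evidence.** The size of the effect rests wholly on assumed inputs, and even the worst row above leaves power at 0.92. That is correct. The arithmetic shows direction and a plausible range, not a demonstrated loss.

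**Convention.** It is tempting to call the definition inconsistent with footnote f of Table 2, where an altered vital sign "is defined as a change of >25% from baseline". That footnote covers only heart rate and blood pressure. The desaturation items on the same form are absolute thresholds, so an absolute band follows the trial's own practice. The case rests on the overlap with eligibility, not on that footnote.

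**Direction.** Randomisation spreads these patients over both arms, so no false benefit is created. True, but a secondary objective biased toward no effect can still be misread as a lack of effect.

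**Conclusion.** The point holds in limited form. As written, the definition counts an eligible patient who is still at 90–94% when the window opens as having respiratory depression, without any change. This inflates incidence in both arms and pulls the comparison toward no effect. The structural part follows from the text alone. The size does not: under assumed shares of 2–10% and assumed true rates of 20% versus 12%, the risk ratio moves from 0.60 to between 0.64 and 0.74, and the real share may be lower.

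A reader might also infer that the trial's main result is compromised or that one arm is favoured. Neither follows. The primary outcome and severe hypoxia lie below the eligibility floor, the sample size does not depend on this outcome, and the expected misclassification is the same in both arms. This is worth correcting in one secondary outcome and no more.

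**What to change.** **Preferred.** Count this outcome as new onset: a fall into the 90–94% band, within the window, from 95% or more at the last reading before induction, taken on study oxygen if that is recorded. Eligibility need not change.

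**Minimum.** Keep the current definition and prespecify, before database lock, a sensitivity analysis restricted to patients with pre-sedation saturation of 95% or more. Report those starting below 95% separately by arm.

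The choice of reference reading matters. Table 3 does not say whether the arrival value is taken on oxygen. A patient at 93% on arrival, 98% on oxygen and 92% under sedation has a genuine event, and an arrival reference would drop it from the main comparison. Hence the last pre-induction value, or the current definition plus the sensitivity analysis.

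**Cost.** One sentence in the outcome definition, or one extra analysis. Vital signs are already scheduled from arrival onward, and saturation is part of standard monitoring in both arms; whether the last pre-induction value is recorded should be confirmed. The denominator for this outcome becomes somewhat smaller: under the assumed shares, 810 per arm would fall to between 794 (810 − 16) and 729 (810 − 81).

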**Step 2: Please DESCRIBE the adverse event(s). Check all that apply.**				
**Minimal risk descriptors**	**Minor risk descriptors**		**Sentinel risk descriptors**	
□ Vomiting/retching	□ Oxygen desaturation (75–90%) for < 60s		□ Oxygen desaturation, severe (<75% at any time) or prolonged (<90% for >60s)	Other, specify below
□ Sub-clinical respiratory depression^a^	□ Apnoea not prolonged		□ Apnoea, prolonged (>60s)	
□ Muscle rigidity, Myoclonus	□ Airway obstruction		□ Cardiovascular collapse/shock^g^	
□ Hypersalivation	□ Failed sedation^e^		□ Cardiac arrest/absent pulse	
□ Paradoxical response^b^	□ Allergic reaction without anaphylaxis			
□ Recovery agitation^c^	□ Bradycardiat^f^			
□ Prolonged recovery^d^	□ Tachycardia^f^			
	□ Hypotension^f^			
	□ Hypertension^f^			
	□ Seizure			

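### Subclinical respiratory depression is a bare SpO2 band tested on its own: read literally it recounts nearly all hypoxic patients, and read by worst category it can rise when falls are halted at 90–94%

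*Protocol article*

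**What the plan says.** The protocol article defines three saturation outcomes over the same window.

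- Primary (Outcomes {12}): "The primary outcome of this study is the incidence of hypoxia (75% ≤ SpO_2_ < 90% for <60 s) in the two groups".
- Secondary: "The incidence of subclinical respiratory depression (90% ≤ SpO_2_ < 95%) in the two groups from the beginning to the end of the operation".
- Secondary: "The incidence of severe hypoxia (SpO_2_ < 75% or 75% ≤ SpO_2_ < 90% for ≥60 s".

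The subclinical outcome has no duration, no reference to the lowest SpO2 and no clause excluding patients who go on to hypoxia. The Objectives section gives the same band.

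The Statistical analysis plan section tests each outcome separately with a χ²-type test: "We intend to compare the incidences of hypoxia, subclinical hypoxia, severe hypoxia, and total hypoxia of the participants". Section {20b} then takes the last of these as its only regression endpoint: "the risk of total hypoxia cumulative incidence was examined using univariable- and multivariable-adjusted logistic regression models". Total hypoxia is not defined in either place.

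Table 2 uses the same term for something else. Its footnote a says that sub-clinical respiratory depression "is defined as capnographic abnormalities suggesting respiratory depression that do not manifest clinically", with no SpO2 band. The form's counting rules also differ from step to step. Step 2 reads "Please DESCRIBE the adverse event(s). Check all that apply", which allows overlap. Step 5 grades by the worst item, for example "If the most serious option(s) checked above are Minimal risk, then this is a Minimal risk adverse event". The label itself changes to subclinical hypoxia in Table 3 and in the analysis section.

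**The concern.** The band can be counted in two ways, and neither gives a usable stand-alone comparison.

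*Literal counting.* A patient who starts at 95% or above and desaturates below 90% passes through 90–95%, and passes through it again on recovery. The outcome is then close to any SpO2 below 95%. A difference between arms may consist only of hypoxia cases already counted in the primary outcome.

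*Worst-category counting.* Each patient is filed once, by the deepest event. Capnography is meant to prompt action before saturation falls below 90%. A patient whose fall is stopped at 92% instead of 86% leaves the hypoxia category and enters the subclinical one, so a better course counts as an extra event against capnography.

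The choice between the two can move a named secondary outcome between benefit, no difference and apparent harm in the same patients. If the choice is made after the data are seen, the result depends on it. The same ambiguity carries into total hypoxia, and so into the only planned odds ratio.

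**Working it through.** **The plan's own figure.** For 8% versus 4%, two-sided 5%, power 0.90 and 1:1 allocation, the two-proportion formula with continuity correction gives 788 per arm. Then 788/0.9 = 876 per arm, or 1752 in total, which is consistent with the stated ~1800. (Without the correction it is 739 per arm and 1644 in total.) This point does not challenge that figure.

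**Inputs from the protocol.** Hypoxia 8% control and 4% capnography, used here as the rate of any SpO2 below 90%. 1800 patients less 10% dropout gives 810 per arm.

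**Inputs not in the protocol (assumptions).**
- s: control rate of patients whose lowest value is 90–94%. Taken as 10%, range 5–30%.
- f: share of the 4 points of prevented hypoxia that stop inside the band, 0 to 1.
- RR: effect of capnography on dips that would only ever have reached 90–94%, 0.5 to 1.

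**Formulas.**
- Worst category: control s; capnography s·RR + 0.04·f.
- Literal band: control s + 0.08; capnography s·RR + 0.04·f + 0.04.
- The worst-category rate rises only if 0.04·f > s·(1 − RR).
- Chance of significance = Φ{[|d| − 1.96·√(2p̄(1−p̄)/n)] / √[(p₁q₁+p₂q₂)/n]}, where d = p₁ − p₂.

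**Worked case, s = 10%, f = 1, RR = 1.** The worst-category rates are 10% and 0.10 + 0.04 = 14%. With p̄ = 0.12 and n = 810, √(2·0.12·0.88/810) = 0.01615, and 1.96 times this is 0.03165. The denominator is √(0.2104/810) = 0.01612. So (0.04 − 0.03165)/0.01612 = 0.518 and Φ = 0.70.

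**Results at s = 10%, 810 per arm.**

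| f | RR | Worst category, control → capnography | Chance significant | Literal band, control → capnography | Chance significant |
|---|---|---|---|---|---|
| 1 | 1 | 10% → 14% | 70%, against | 18% → 18% | no difference |
| 0.5 | 1 | 10% → 12% | 25%, against | 18% → 16% | 19%, for |
| 1 | 0.75 | 10% → 11.5% | 16%, against | 18% → 15.5% | 27%, for |
| 1 | 0.5 | 10% → 9% | 10%, for | 18% → 13% | 79%, for |
| 0 | 1 | 10% → 10% | no difference | 18% → 14% | 59%, for |
| 0 | 0.75 | 10% → 7.5% | 43%, for | 18% → 11.5% | 96%, for |

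Over the range of s with f = 1 and RR = 1, the chance of significance against capnography is 88% at s = 5% (89% by simulation) and 41% at s = 30%.

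**Turning point.** With f = 1 the rise disappears once RR falls to 1 − 0.04/s: 0.60 at s = 10%, 0.80 at 20%, 0.87 at 30%.

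**Double count under the literal rule.** The hypoxic share of control events is 0.08/(s + 0.08): 8/18 = 44% at s = 10%, 62% at 5%, 21% at 30%. In the row f = 0, RR = 1, the number of band-only patients is the same in both arms, so the whole 18% → 14% difference is hypoxia counted again.

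**Total hypoxia at s = 10%.** Defined as any SpO2 below 90%, the odds ratio is (0.04/0.96)/(0.08/0.92) = 0.48. If the 90–94% band is included, it is (0.14/0.86)/(0.18/0.82) = 0.74 with f = 0, RR = 1, and 1.0 with f = 1, RR = 1.

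**The case against.** The strongest reply is that the literal reading is not what the authors mean. The label implies depression that stopped short of hypoxia. The bands adjoin, a separate total suits categories that add up, and Step 5 of Table 2 grades by the worst item. A per-patient derivation rule could sit in an analysis plan or CRF guide that is not shown. On that reading the double count goes away. This is fair, but it leads to the worst-category reading, whose stand-alone test has the migration problem. That test is fixed in the protocol itself.

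A reader might infer that the worst-category outcome rises whenever capnography works. The document does not support that. The Participant timeline section lists apnea and altered ventilation as prompts for action without any SpO2 condition, so capnography may also prevent some dips to 90–94%. RR = 1 is therefore one case among several, and the rate can fall, as the table shows. The documents give no value for s, f or RR.

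Nor can one say that every hypoxic patient is counted again. A fast fall could skip the band between readings. Eligibility excludes only SaO2 below 90%, so a patient may start inside the band and meet the definition with no sedation effect. That second case is a further weakness of the definition.

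Finally, all categories would be reported side by side, so a shift from hypoxia to subclinical could be seen by an attentive reader. That limits the harm but does not make the separate p-value interpretable.

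**Conclusion.** The point holds in this form: the outcome is a saturation band with no counting rule, tested alone, and its direction cannot be read as benefit or harm. Literal counting recounts nearly all hypoxic patients (44% of control events at s = 10%; 21–62% for s from 30% down to 5%). Worst-category counting can rise under an effective intervention, but need not. The 70% chance of a significant result against capnography rests on s = 10%, f = 1 and RR = 1, and is an illustration, not a forecast.

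A reader might also infer that the planned odds ratio will be near 1 even if hypoxia is halved. That requires total hypoxia to include the 90–94% band, which the document does not state, together with f = 1 and RR = 1. What can be said is that the only modelled endpoint is undefined, and that including the band would dilute it.

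The conflict with footnote a of Table 2 needs no assumption: one term has two definitions. The primary outcome, its power and the sample size are not affected. This should be corrected before the data are analysed, but it does not threaten the main comparison.

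**What to change.** 1. Compare cumulative thresholds between arms: any SpO2 below 95%, any SpO2 below 90%, and severe hypoxia. Moving a patient to a milder category cannot raise any of these. Alternatively, classify each patient once (none, 90–94% only, hypoxia, severe) and test that ordered variable a single time.
2. Show the 90–94%-only category descriptively, without its own superiority test.
3. Define total hypoxia, in the Statistical analysis plan section and in {20b}, as any SpO2 below 90%.
4. Reconcile the secondary outcome with footnote a of Table 2, and use one label throughout.

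The cost is wording in the secondary outcomes, the analysis section, {20b} and Table 2, plus one variable derived from SpO2 data already recorded. The small downside is that the subclinical category loses its stand-alone p-value.
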